## Methods

### Data Collection

#### Setting and Participants

This is a quasi-experimental study. This protocol is version 1.0, finalized on July 8, 2025. We will select children with malignant tumors and their family caregivers who were hospitalized at West China Second Hospital, Sichuan University, between July 2025 and December 2026. Family caregivers of the children will be enrolled. The researchers will provide a detailed description of the study’s purpose and content to the participants, who must sign an informed consent form.

The QR code for the web-based questionnaire will be distributed after caregivers provide informed consent. The family caregivers recruited for the study will be divided into control and intervention groups. Children will be grouped according to their diagnosis and treatment timeline as follows: children admitted from July to December 2025 will form the control group, and those admitted from July to December 2026 will form the intervention group. The caregivers of the children will be enrolled along with the children. In the intervention group, the intervention program will be implemented after inclusion. For the control group, where routine health promotion is implemented, an intervention program based on FCEM will be offered upon the second admission to the hospital (Figure 1).

**Figure 1 figure1:**
[figure not shown]
Participant timeline.

After the family caregivers complete the baseline survey, the researchers will distribute paperwork or provide verbal health promotion with relevant health promotion components and assess the caregivers’ knowledge weekly.

The questionnaire will be re-administered 3 days before the child is discharged. One researcher will enter the data, which will be double-checked for errors by another researcher. After all data are entered, the analysis will be performed by a designated specialist who remains unaware of the groupings. Finally, 2 additional researchers will independently review the analyses to ensure accuracy. Family caregivers will be aware of their grouping. If family caregivers prefer to adjust their groupings, appropriate adjustments will be made based on their identified needs.

The inclusion criteria are as follows: (1) children aged 0-18 years, (2) children clinically diagnosed with malignant neoplasms, and (3) first-time visitors to our hospital.

The exclusion criteria are as follows: (1) children diagnosed and treated with radiotherapy or chemotherapy in other hospitals and (2) children undergoing their first treatment in our hospital for recurrence of the disease.

Primary caregiver inclusion criteria are as follows: (1) the caregiver is enrolled along with the child, (2) the caregiver is aged 18 years or older, (3) the caregiver is a member of the child’s immediate family, (4) the caregiver has cared for the child for the longest period among multiple caregivers, (5) the caregiver has basic communication and reading skills and is proficient in Chinese, and (6) the caregiver has no previous history of psychiatric illness or consciousness-related disorders.

The sample size was calculated to be 128 using G*POWER 3 software [10] with the parameters α=.05, 1 – β=0.8, and effect size=0.5. Considering a 10% lost-to-follow-up rate, the total sample size required was estimated to be 142, with 71 caregivers in the intervention group and 71 in the control group.

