### Objectives

This study aims to recruit family caregivers of children with malignant neoplasms to develop a corresponding intervention program based on the FCEM and to evaluate its impact on caregiving preparedness and caregiving capacity. Additionally, the study aims to examine the effects of the empowerment intervention on caregivers’ self-efficacy as well as their levels of depression, anxiety, and stress.

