### Research Hypotheses

This study has the following research hypotheses:

Statistically significant differences in caregiver preparedness and caregiving capacity will occur after the FCEM intervention program.Significant differences in self-efficacy, depression, anxiety, and stress will occur in the intervention group after the intervention compared to previous measurements.

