#### Dependent Variables

The outcome variables are caregiving preparedness, caregiving capacity, self-efficacy, depression, anxiety, and stress. The tools used to measure these variables are described in Table 1.

The caregiver preparedness scale was developed by Archbold et al [11] to assess parents’ caregiving preparedness. This scale consists of 8 items, namely, preparedness for physical needs, emotional needs, service planning, caregiving stress, comfort care, coping with and managing emergencies, accessing medical information resources and help, and overall caregiving preparedness [11]. A 5-point Likert scale was used, with scores ranging from 0-4 indicating “not at all prepared” to “fully prepared,” and higher scores reflecting better preparedness for caregiving. Yanjin et al [12] adapted the scale for use in China, demonstrating its good reliability and validity as a suitable tool for assessing preparedness. The Cronbach α of the Chinese version was 0.92 [12].

**Table 1 table1:** Measurement tools used to assess outcome variables.

Tool	Dimensions	Items
Caregiver preparedness scale	Physical care, emotional support, in-home support services, and caregiving stress	8
Family caregiver task inventory	Adaptation to caregiving roles, coping and assistance provision, management of personal emotions, caregiving needs, and assessment of family and social resources	25
General self-efficacy scale	Self-efficacy	10
Depression anxiety stress scale-21	Depression, anxiety, and stress	21

Caregiving capacity was measured using the family caregiver task inventory developed by Clark and Rakowski [13] in 1983, which covers 5 dimensions: role adaptation, caregiving assistance, emotional management, life adjustment, and use of social and family resources. It consists of a total of 25 items. The family caregiver task inventory uses a 3-point Likert scale, with 0 indicating “no difficulty,” 1 indicating “some difficulty,” and 2 indicating “great difficulty.” Higher scores represent greater difficulty and poorer caregiving capacity. The Cronbach α of the Chinese version was 0.86 [14].

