### Data Analysis

Data will be analyzed using SPSS version 26.0 (IBM Corporation). For general information, measurement data conforming to a normal distribution will be described by means and SDs, and count data will be described by frequencies and constitutive ratios. Missing data will be removed and will not be included in the analysis. Participants who request to switch groups based on their preferences will be excluded from the primary analysis; however, we will summarize the baseline characteristics of these participants and compare them to those who remain in their originally assigned groups. This comparison will include demographics to assess the potential impact of nonrandom attrition on study validity.

Independent-sample *t* tests will be used to compare caregiving preparedness, caregiving capacity, self-efficacy, and depression, anxiety, and stress scores between the 2 groups before the intervention. After the intervention, both within-group and between-group differences in these variables will be analyzed using independent-sample *t* tests, paired *t* tests, Mann-Whitney tests, and paired rank-sum tests.

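### The sample size supports one comparison, but the first hypothesis names two outcomes and the protocol gives no primary outcome, time point or success rule

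*Protocol article*

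**What the plan says.** Methods, Setting and Participants, gives one calculation: "The sample size was calculated to be 128 using G*POWER 3 software", using "parameters α=.05, 1 – β=0.8, and effect size=0.5". It continues: "Considering a 10% lost-to-follow-up rate, the total sample size required was estimated to be 142". This is split equally, 71 per group. No outcome, scale, test or assessment time is attached to it.

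The Objectives section states the main aim as "to evaluate its impact on caregiving preparedness and caregiving capacity", and then adds self-efficacy, depression, anxiety and stress as further effects to examine. The first item under Research Hypotheses reads "Statistically significant differences in caregiver preparedness and caregiving capacity will occur after the FCEM intervention program". The other four outcomes come in a second hypothesis, which is worded as a within-group change.

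Under Dependent Variables all six stand in one unranked list: "The outcome variables are caregiving preparedness, caregiving capacity, self-efficacy, depression, anxiety, and stress". Data Analysis plans within-group and between-group tests on all six and states no significance level. It uses the word primary once, for caregivers who switch group and "will be excluded from the primary analysis", without saying which outcome or contrast that analysis concerns. Follow-Up Assessment adds a 1-month measurement with the same instruments.

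**The concern.** A power statement holds for a specified comparison. This one fits a single test, while the leading hypothesis covers two outcomes. The text leaves open what would count as success: both outcomes differing, either one, or each reported as its own claim. It also leaves open whether the pre-discharge or the 1-month assessment decides.

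The choice matters because each rule spoils a different stated property. If both must differ, 80% power is not reached. If either is enough, the 5% error rate is not kept. With the rule unstated, a reader of the results could not tell whether the trial met its aim, and the more favourable of the two outcomes could become the headline after the data are seen.

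**Working it through.** **Inputs from the article:** alpha .05, power 0.80, effect size 0.5 (read as a standardised mean difference), 1:1 allocation, 10% loss; two outcomes in the main aim; six outcomes in all.

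**Assumptions:** a two-sided independent-samples t test, since neither the test nor its sidedness is given for the calculation; d = 0.5 for both main outcomes; correlations between outcomes, shown as a range because none is given; .05 for each test, because the sample-size sentence holds the only alpha in the article.

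**1. The plan's own figure.** Non-central t, d = 0.5, two-sided .05, power 0.80: 63.8, so 64 per arm and 128 in total. Power at 64 per arm is 0.801. A one-sided test would need 102, which does not match. Loss: 128 / 0.9 = 142.2, stated as 142. The arithmetic is sound for one test. If all 71 per arm are retained, power for one test is 0.841.

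**2. Both main outcomes must differ, each at .05.** If independent, joint power is the product: 0.801 × 0.801 = 0.64 at 64 per arm and 0.841 × 0.841 = 0.71 at 71 per arm. With correlation r, it is the bivariate normal probability that both statistics exceed their critical value.

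| Correlation (assumed) | 64 per arm | 71 per arm |
|---|---|---|
| 0 | 0.64 | 0.71 |
| 0.5 | 0.69 | 0.74 |
| 0.9 | 0.75 | 0.80 |

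**3. Either outcome suffices, each at .05, no true effect on either.** If independent: 1 − 0.95² = 0.0975. At correlation 0.5 it is about 9%, at 0.7 about 8.3%, and at 0.9 about 7%.

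**4. Either suffices, alpha split to .025 each.** Power per outcome is 0.712 at 64 per arm and 0.761 at 71 per arm.

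**5. Each outcome claimed separately at .05.** Power is 0.801 for each, as stated. The chance of at least one false claim is then that of step 3.

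**6. All six outcomes, if every null is true and each is tested at .05.** If independent: 1 − 0.95⁶ = 0.265. Simulation gives about 21% at a common correlation of 0.5 and 16% at 0.7.

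**7. What baseline adjustment could return.** Adjusting for a baseline score with baseline-to-post correlation ρ divides the residual SD by 1/√(1 − ρ²), so the effective effect size becomes 0.5 / √(1 − ρ²). For ρ = 0.3 this is 0.5 / √0.91 = 0.524; for ρ = 0.5 it is 0.5 / √0.75 = 0.577. At 64 per arm and alpha .025, power is then 0.76 and 0.84, against 0.71 unadjusted. The article gives no value for ρ.

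**The case against.** The best defence is that the first hypothesis states neither a both-must-succeed nor an either-suffices rule. If preparedness and capacity are simply two separate claims, the calculation does give 80% power for each. That is right. The consequence is that the fault becomes one of error control, because nothing then limits the chance of a false claim across the pair. The defence also points out that the lower power figures assume the whole 10% allowance is used up. That is fair too, which is why the 71-per-arm figures are shown.

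Methods of adjustment may sit in an analysis plan that is not shown, and their absence from an article is no fault. But which outcome the sample size serves is a design decision, and an adjustment method written elsewhere would not change the power printed here.

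A reader might go further and infer that the trial makes six equal confirmatory claims at .05, so that some outcome will probably turn up significant by chance. The documents do not support that. Objectives and Research Hypotheses already set self-efficacy, depression, anxiety and stress below the main pair. Data Analysis states no level for any test. And 16-26%, which itself requires every null to be true, is an upper bound and well short of probable.

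**Conclusion.** The point holds for the two main outcomes. The 128 is correct for one two-sided t test but is tied to no named outcome, time point or rule, while the first hypothesis covers two outcomes. Depending on the rule adopted, one of the following applies:

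- joint power of about 0.64-0.75 (0.71-0.80 if nobody is lost);
- power of 0.71 per outcome with alpha split (0.76 if nobody is lost);
- an error rate of about 7-10% if either suffices at .05, or if each is claimed separately with 80% power.

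These figures rest on d = 0.5 for both outcomes, assumed correlations from 0 to 0.9, and .05 carried over from the sample-size sentence. It should be put right, but the trial's size is not in itself at fault: with one outcome named as primary, 142 stands.

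**What to change.** Before any between-group comparison is made, the sponsor should choose one of two routes and amend the hypotheses, sample-size and analysis text to match.

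- **One primary outcome.** Name either caregiving preparedness or caregiving capacity; the article does not rank one above the other, so the choice is the sponsor's. Define it as the baseline-adjusted between-group difference at the pre-discharge assessment, tested at .05. Test the other next, at .05, only if the first succeeds. The 142 is unchanged.
- **Two co-primary outcomes.** State whether both or either must succeed, and restate the power: about 0.64-0.75 at 64 per arm if both are required, or 0.71 per outcome at alpha .025 if either suffices.

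Under both routes, label self-efficacy, depression, anxiety and stress as secondary or exploratory, which formalises the order already present in the Objectives.

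Baseline scores are already collected, so adjustment needs no new data. Any gain in power should be stated as conditional on the baseline-to-post correlation.

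The cost is wording, plus one real concession: either one outcome takes priority over the other, or a less favourable power is printed. Neither route requires enlarging the trial.

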#### Sociodemographic Variables

Sociodemographic variables in patients (including age, sex, ethnicity, medical payment method, clinical diagnosis, and duration of disease) and their caregivers (including age, relationship with the patient, ethnicity, place of residence, number of children, marital status, level of education, occupation, monthly family income, caregiving experience, number of other persons in need of care, hours of care per day, health status, disease awareness, and access to information) will be recorded. Disease-related variables will be obtained from the consent forms signed by the patients and their guardians.

#### Dependent Variables

The outcome variables are caregiving preparedness, caregiving capacity, self-efficacy, depression, anxiety, and stress. The tools used to measure these variables are described in Table 1.

The caregiver preparedness scale was developed by Archbold et al [11] to assess parents’ caregiving preparedness. This scale consists of 8 items, namely, preparedness for physical needs, emotional needs, service planning, caregiving stress, comfort care, coping with and managing emergencies, accessing medical information resources and help, and overall caregiving preparedness [11]. A 5-point Likert scale was used, with scores ranging from 0-4 indicating “not at all prepared” to “fully prepared,” and higher scores reflecting better preparedness for caregiving. Yanjin et al [12] adapted the scale for use in China, demonstrating its good reliability and validity as a suitable tool for assessing preparedness. The Cronbach α of the Chinese version was 0.92 [12].

**Table 1 table1:** Measurement tools used to assess outcome variables.

Tool	Dimensions	Items
Caregiver preparedness scale	Physical care, emotional support, in-home support services, and caregiving stress	8
Family caregiver task inventory	Adaptation to caregiving roles, coping and assistance provision, management of personal emotions, caregiving needs, and assessment of family and social resources	25
General self-efficacy scale	Self-efficacy	10
Depression anxiety stress scale-21	Depression, anxiety, and stress	21

Caregiving capacity was measured using the family caregiver task inventory developed by Clark and Rakowski [13] in 1983, which covers 5 dimensions: role adaptation, caregiving assistance, emotional management, life adjustment, and use of social and family resources. It consists of a total of 25 items. The family caregiver task inventory uses a 3-point Likert scale, with 0 indicating “no difficulty,” 1 indicating “some difficulty,” and 2 indicating “great difficulty.” Higher scores represent greater difficulty and poorer caregiving capacity. The Cronbach α of the Chinese version was 0.86 [14].

The general self-efficacy scale was developed by Schwarzer et al [15] in 1981 and subsequently translated into Chinese [15,16]. The general self-efficacy scale assesses the self-efficacy of family caregivers. It contains 10 items within the single dimension of self-efficacy and is scored on a 4-point Likert scale, ranging from 1 (“not at all true”) to 4 (“exactly true”), with a total score of 10 to 40. Higher scores indicate better general self-efficacy [15,16]. The Cronbach α coefficient for this scale was 0.91 [15].

The depression anxiety stress scale-21 was developed by Lovibond and Lovibond [17] in 1995 and later translated into Chinese by Gong et al [18]. The depression anxiety stress scale-21 evaluates depression, anxiety, and stress levels in family caregivers. It contains 21 items across 3 dimensions: depression, anxiety, and stress. The depression subscale includes items 3, 5, 10, 13, 16, 17, and 21; the anxiety subscale includes items 2, 4, 7, 9, 15, 19, and 20; and the stress subscale includes items 1, 6, 8, 11, 12, 14, and 18. A 4-point Likert scale is used, with scores ranging from 0 (“did not apply at all”) to 3 (“applied most or all of the time”). Higher scores indicate higher levels of depression, anxiety, and stress. The Cronbach α coefficient of the scale was 0.89 [18].

#### Intervention Program

##### Intervention Content Development

Through a preliminary search of the literature, the caregiving needs of family caregivers of children with malignant neoplasms were identified to include disease information needs, such as knowledge about the disease, its progression, and prognosis; symptom management needs, including knowledge related to Peripherally Inserted Central Catheter (PICC) or infusion port care; dietary management needs; prevention and treatment of infections; management of daily living activities; prevention and treatment of adverse reactions to chemotherapy drugs; and psychological regulation needs, such as managing anxiety, nervousness, and fear.

We plan to select approximately 17 caregivers of children with malignant neoplasms for interviews using purposive sampling as part of the preliminary research. Face-to-face interviews using open-ended questions will be conducted by experienced interviewers. The interview is expected to last 15-30 minutes. It will be discontinued immediately if the child requires medical attention. The interview outline includes the following questions:

What kinds of feelings do you experience during caregiving, and what are your biggest concerns and stresses?What problems or needs have you encountered in the caregiving process, and how have you coped with them?Regarding treatment and care, what kind of health guidance would you like medical workers to provide (including knowledge about diseases, dietary management, daily life activities management, maintenance of PICCs and infusion ports, and knowledge of drug reactions)?

Data collection will be discontinued when thematic saturation is reached. Saturation is defined as the point at which no new themes or codes emerge from at least 2 consecutive interviews. The results of interviews with 17 caregivers will be summarized and refined to determine the main needs of the caregivers. The results of a previous pilot study on parents of children with acute lymphoblastic leukemia showed that the main needs of caregivers were in the following areas:

Disease information, including symptoms and manifestations, incidence rate, relapse rate, cure rate, 3-year to 5-year survival rate, and other disease-related details.Infusion port and PICC maintenance, including precautions after infusion port implantation, PICC-related knowledge, and daily observation priorities.Infection prevention, including methods for infection prevention and management.Medication guidance, including common adverse drug effects and steps to observe and manage them.Dietary guidance, including methods for preparing hygienic and appropriate meals for children.Psychological aspects, including methods to alleviate negative emotions, such as anxiety and depression, in caregivers and children.

A draft intervention program will be developed based on the FCEM model, literature review, results of the preliminary research, and the departmental health education manual (Multimedia Appendix 1).

##### Intervention Revision

After the first draft is finalized, a group meeting is planned for the researchers and team members, all of whom are clinical and nursing experts in pediatric hematology. The group includes a hematologist and 5 nursing staff members with more than 5 years of experience. Before the study begins, a group meeting will be held to jointly negotiate the terminology to be used with patients during implementation and to ensure that the terminology used during implementation is harmonized.

#### Intervention Delivery Process

##### Intervention Group

The intervention group will be provided with a family empowerment intervention program based on usual care.

Three sessions of approximately 15-30 minutes each will be conducted within 3 days of the child’s admission to the hospital, from the fourth day to 3 days before discharge. The timing of the intervention sessions was determined based on evidence from a prior study conducted in China involving caregivers of children with asthma combined with clinical experience [19]. The researcher or charge nurse will assess the caregivers’ knowledge every week using uniform evaluation criteria and adjust the topic or number of interventions within each phase based on the knowledge gained, with the final intervention content and timeline remaining unchanged.

During stage 1 (within 3 days of admission), the researchers will explain the use of the facilities in the ward, including the proper use of a hospital bed or laminar flow bed, and outline safety precautions in the ward (including preventing falls, falls out of bed, and avoiding burns). They will also provide information about daily care, infection prevention, dietary considerations (eg, low-fat diets and special diets for children experiencing vomiting), input and output monitoring, the recognition of symptoms for oral and perianal infections and how to gargle and cleanse the perianal area, and disease-related information, including cure rates and recurrence rates. Completing stage 1 will require 15-25 minutes.

During stage 2 (fourth day after admission to 3 days before discharge) the nurse in charge will ask the main caregiver about difficulties and problems encountered during the caregiving process using open-ended questions, such as “In your opinion, what is the most difficult thing right now?” “Do you have difficulties taking care of your children and yourself?” “What kind of information would you like the nurse to provide more of while providing care for your child?” Based on the preinterview, the nurse will conduct adequate communication with the main caregiver in response to their difficulties, listen patiently, and provide positive guidance tailored to their psychological state. A childcare program will be developed, and the following content will be explained to the patient’s family, part of which will be presented in written or video form: (1) medication guidance based on the actual use of drugs by the child, including the dosage, frequency, and adverse effects of the drugs; (2) PICC-related knowledge, including daily observation, handling of abnormalities, prevention and identification of complications, and precautions for daily life and exercise; (3) postoperative care for infusion port implantation, including postoperative diet, postoperative medication changes, observation during use, and postdischarge precautions; (4) blood indicators, including an explanation of blood indicators, such as platelets, hemoglobin, and neutrophils, along with precautions to be taken in case of critical values; (5) condition monitoring and emergency treatment, including simple treatments in case of fever or other emergencies; and (6) psychological support, including sharing stories of other successful cases to positively motivate the caregivers. Completing stage 2 will require 20-30 minutes.

Stage 3 (3 days before discharge) will involve the evaluation of outcomes and discharge instructions as well as communication with the patient to address problems related to caregiving abilities and caregiving preparedness, affirm the level of care provided by the family caregiver during the child’s hospitalization, boost their confidence, and guide the child’s postdischarge medication, nursing care, review, and follow-up chemotherapy plans. Completing stage 3 will require 10-20 minutes.

Stage 4 encompasses the entire implementation process. During program implementation, a dedicated researcher will coach the primary caregiver 1-on-1 to ensure they understand the program content (ie, until they can repeat it independently). Family caregivers will be instructed to record changes in their children’s symptoms. The family caregivers’ knowledge of the program will be assessed weekly (Multimedia Appendix 2).

